### Procedures and study flow

*Eligibility Screening, Informed Consent, and Baseline Assessment (T1).* Interested individuals will contact the study team via email or phone. The principal investigator will then call potential participants to confirm eligibility criteria. Participants will be recruited in cohorts of 20–30 physicians, who will be randomly assigned to either the BEST group or the WLC, allowing for our desired mindfulness group size of 10–15 participants. Screening will continue until we have an adequate number of eligible, interested, and available participants for the next cohort.

All eligible participants will then review and verbally acknowledge the IRB-approved consent form. After obtaining consent and enrollment, participants will be automatically emailed a link to complete the study questionnaires through Qualtrics. They will also receive an at-home blood collection kit in the mail to provide a blood sample for immune evaluation. Participants will be advised to complete the blood collection in the morning to control for diurnal variations in immune parameters. Based on pilot completion data, the questionnaire battery takes approximately 20–30 minutes, and blood specimen collection requires approximately 10 minutes. Baseline assessments will be conducted during the 2 weeks preceding the first class of the intervention. The principal investigator conducts eligibility screening and consent, and the distribution of assessment links is automated through Qualtrics.

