### Intervention conditions

*General Information.* The experimental mindfulness intervention is a manualized six-session (60 minutes each) protocol designed for in-person or remote delivery by trained mindfulness instructors. The intervention will be group-based and delivered remotely via Zoom. Based on input from our community advisors, the group sessions will be conducted during the workday (around lunchtime).

*Building Emotional Strength Training (BEST).* [name], Director of UCLA Mindful, developed the intervention drawing on her substantial experience working with meditation practitioners and her expertise in designing group-based mindfulness courses for diverse audiences [74]. Notably, the research team consulted with several physicians to determine the most suitable format, including class length, scheduling, and mode of delivery, to ensure the intervention was feasible and appropriate for our target population. These consultations informed the decision to deliver BEST remotely via videoconference, in shortened sessions scheduled at times that accommodate physicians’ clinical demands, to design a program that could fit within the busy schedule of a full-time physician.

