During each session, participants receive structured training and instruction in meditation exercises, including theoretical background, formal guidance on the day’s topic, and question-and-answer sessions to support learning. Additionally, participants will be guided through each meditation exercise introduced during class. Furthermore, each class will include dyadic discussions, allowing participants to interact directly with one another. The sessions will introduce the following topics and associated practices: 1) introduction to mindfulness, 2) mindfulness and self-compassion, 3) self-directed kindness, 4) compassion, 5) equanimity, and 6) joy. The BEST intervention also includes home practice, in which participants are encouraged to practice the meditation technique introduced in class at home, starting with five minutes and gradually increasing to 20 minutes per day throughout the six weeks of the intervention. All sessions will be delivered by the intervention developer, who has nearly 30 years of experience teaching meditation.

*Waitlist Control (WLC).* The WLC will control for naturally occurring changes in the outcomes and mediators over the assessment period. Participants in this group will not engage in any study-related activities outside of the remote assessments (baseline, mid-course, and post-intervention). Participants randomized to this condition will be offered the BEST intervention after all data collection is completed.

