### Sample size

*Primary and secondary outcome analyses.* Typical effect sizes from randomized controlled trials of MBIs with passive control groups range from ds = 0.10–0.89, with trials in healthcare populations achieving an average effect size of 0.39 and digitally delivered interventions achieving an average effect size of 0.54 [124]. Recruitment capacity for the current trial was 90 participants, given financial and time constraints. Accordingly, we report the minimum detectable effect with 80% power for the primary outcome, perceived stress at the post-intervention assessment, comparing the mindfulness condition with the waitlist control (WLC). The minimum detectable effect was estimated using G*Power [125] for the primary analysis of covariance (ANCOVA; fixed effects, a two-level between-subjects factor, and one covariate), with the baseline value of the outcome entered as the covariate, α = 0.05, power = 0.80, and one numerator degree of freedom. Assuming a baseline–post correlation for PSS of r = 0.50 and the anticipated enrolled sample of 90 participants (45 per condition), of whom approximately 72 are expected to provide complete outcome data after accounting for ~19% attrition, based on a meta-analysis of overall and differential attrition across 114 randomized MBI trials in clinical and non-clinical populations [126], the study provides 80% power to detect a between-group effect of d = 0.58 (Cohen’s f = 0.34). This effect is comparable to the average effect of digitally delivered MBIs relative to passive control conditions (d = 0.54) [124], indicating that the trial is powered to detect effects of the magnitude typically observed for remotely delivered MBIs. In sensitivity analyses varying the baseline–post correlation from r = 0.40 to 0.60, the minimum detectable effect ranged from d = 0.53 to 0.61. The trial is powered for the primary comparison on perceived stress at the post-intervention endpoint. Analyses of secondary outcomes (burnout, depressive symptoms, inflammatory biomarkers, psychological well-being, and sleep quality) will provide estimates of intervention effect sizes but are not powered for definitive hypothesis testing.

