All outcome models adjust for a pre-specified set of covariates, determined a priori on substantive grounds rather than on observed baseline balance. For each outcome, the primary ANCOVA includes the baseline (T1) value of that outcome as a covariate. Additionally, analyses for inflammatory markers will control for variables known to influence inflammation (e.g., BMI). In keeping with our preregistered analysis plan and CONSORT guidance, covariates are held fixed across analyses regardless of any observed baseline differences between conditions. All primary and secondary outcomes are continuous and assessed at multiple time points. The primary hypothesis concerns the between-condition difference in each outcome at the post-intervention endpoint. Accordingly, the primary analysis will be an ANCOVA comparing conditions (BEST vs. WLC) for each outcome at the post-intervention endpoint, adjusting for baseline (T1) values. ANCOVA is specified a priori as the primary model based on the study design. Covariates are pre-specified as described above. Perceived stress is the single confirmatory primary outcome and is tested at α = 0.05, requiring no adjustment for multiplicity. The secondary outcomes (burnout, depressive symptoms, psychological well-being, sleep quality, and inflammatory biomarkers) are pre-specified but interpreted as exploratory. These analyses will provide effect-size estimates and are reported without formal confirmatory claims or adjustment for multiple comparisons, informing future adequately powered trials rather than definitively testing efficacy.

We anticipate approximately 19% attrition based on comparable mindfulness-based intervention trials [126], and the extent and reasons for missing outcome data will be reported by condition in the CONSORT flow diagram. Our analyses assume that data are missing at random (MAR) conditional on baseline covariates and observed outcomes, an assumption supported by the collection of baseline and intermediate measures likely to predict missingness. To maintain the ITT principle under this assumption, missing endpoint data will be addressed using multiple imputation [134], with ANCOVA estimates pooled across imputed datasets according to Rubin’s rules [135].

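### BEST is taught in about three to four classes and the waitlist in none, but the primary ANCOVA and the detectable effect of d = 0.58 allow for no within-class correlation

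*Protocol article*

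**What the plan says.** Randomisation is of individuals. Procedures and study flow says: "Participants will be recruited in cohorts of 20–30 physicians, who will be randomly assigned to either the BEST group or the WLC", this "allowing for our desired mindfulness group size of 10–15 participants". Intervention conditions describes the BEST arm: "The intervention will be group-based and delivered remotely via Zoom", and "each class will include dyadic discussions, allowing participants to interact directly with one another". One person teaches every class: "All sessions will be delivered by the intervention developer". Of the waitlist it says: "Participants in this group will not engage in any study-related activities outside of the remote assessments".

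The primary model in the Data analysis plan has two terms, condition and the baseline value of the outcome: "the primary analysis will be an ANCOVA comparing conditions (BEST vs. WLC) for each outcome at the post-intervention endpoint, adjusting for baseline (T1) values". The sensitivity mixed model in the same section has a random intercept for the participant only. Robust standard errors are mentioned there only as a remedy for non-normality.

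Under Sample size, "the study provides 80% power to detect a between-group effect of d = 0.58", from a two-group ANCOVA with one covariate, baseline–post correlation 0.50 and about 72 completers. The Discussion repeats 0.58. Neither the power calculation nor the analysis mentions class, ICC or a design effect.

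**The concern.** The design is partially nested. People in the same BEST class share sessions, group composition and discussion partners, so their outcomes may be correlated. Waitlist participants have no such link. An analysis that treats all participants as independent leaves the between-class variance out of the standard error of the treatment contrast.

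This differs from a cohort or calendar effect common to both arms. A cohort term removes what the two arms of a cohort share, whereas a class effect present only in BEST remains.

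Two statements are at stake. Perceived stress is the single confirmatory test, at two-sided 0.05, so an understated standard error gives too narrow an interval and too many false positives. The Sample size section also compares 0.58 with an average of 0.54 for digitally delivered programmes and concludes that the trial is powered for effects of that typical size. Since 0.58 already exceeds 0.54, any positive ICC weakens that conclusion further.

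**Working it through.** **Inputs from the article.** 45 randomised per arm; about 72 completers, so 36 per arm; r = 0.50; two-sided α = 0.05; power 0.80. Classes of 10–15 give 45/15 = 3 to 45/10 = 4.5 classes. I use 3 classes (36/3 = 12 completers each) and 4 classes (36/4 = 9 each).

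**Assumption.** The article gives no ICC. I take 0.01, 0.05 and 0.10, as a share of the residual variance after baseline adjustment, in BEST only.

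**Step 1: reproduce the stated figure.** Noncentral F with 1 and 69 df and λ = 72f², solved for 80% power, gives f = 0.335. Then d = 2f√(1 − r²) = 2 × 0.335 × √0.75 = 0.58. The stated value reproduces exactly under independence, so it is the ICC = 0 figure.

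**Step 2: inflate the BEST-arm variance.** With m completers per class, the design effect in BEST is DE = 1 + (m − 1) × ICC. The waitlist keeps 1. With equal arms, the standard error of the contrast and the detectable effect are both multiplied by √((DE + 1)/2). Example with 3 classes and ICC 0.05: DE = 1 + 11 × 0.05 = 1.55; √(2.55/2) = 1.129; 0.58 × 1.129 = 0.65.

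| Classes | ICC | DE | SE factor | Detectable d | Type I error |
|---|---|---|---|---|---|
| 3 | 0.01 | 1.11 | 1.027 | 0.60 | 5.6% |
| 3 | 0.05 | 1.55 | 1.129 | 0.65 | 8.3% |
| 3 | 0.10 | 2.10 | 1.245 | 0.72 | 11.5% |
| 4 | 0.01 | 1.08 | 1.020 | 0.59 | 5.5% |
| 4 | 0.05 | 1.40 | 1.095 | 0.64 | 7.4% |
| 4 | 0.10 | 1.80 | 1.183 | 0.69 | 9.8% |

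Type I error here is 2(1 − Φ(1.96/SE factor)). These figures treat the ICC as known and include no loss of degrees of freedom.

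**Step 3: simulation.** 20,000 trials per setting, analysed with the planned ANCOVA, rejected a zero average effect in 5.6–5.7% (ICC 0.01), 7.2–8.0% (0.05) and 9.7–11.6% (0.10). Adding cohort fixed effects gave 5.6–5.7%, 7.7–8.4% and 10.2–11.5%, so a cohort term does not repair it.

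**Step 4: what a fitted partially nested model would cost.** With Satterthwaite df (k − 1 for the k classes in BEST, 35 in the waitlist), the width of the 95% interval relative to the ANCOVA is SE factor × t(df)/t(69), where t(69) = 1.995:

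- ICC 0: 17% wider with 3 classes, 10% with 4
- ICC 0.05: 43% and 25% wider
- ICC 0.10: 69% and 40% wider

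**The case against.** A reader might infer that the standard error is wrong as a matter of fact and that the false-positive rate exceeds 5%. The article does not support that. Everything depends on an ICC above zero, and several features favour a small one: a single instructor, a manual, six one-hour remote sessions, individual home practice and recruitment across healthcare systems. At ICC 0.01 the detectable effect moves only to 0.59–0.60, inside the 0.53–0.61 that the article already shows for other baseline correlations. This stands, and it makes the point conditional. It does not remove it, because shared sessions and dyads remain and zero is nowhere stated as an assumption.

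The type I claim also needs a particular null. If BEST affects nobody, no BEST-only class effect arises and the ANCOVA keeps its level. Inflation requires class effects that differ but average to zero over classes that might have been run. That matters if the result is to speak for the programme beyond these three or four classes, as the Discussion does when it looks to other stressed populations.

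A common cohort effect, if arms are balanced within cohorts, would make the unadjusted standard error slightly too large and could partly offset the problem.

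Nor is 0.58 an arithmetic error, and no sample-size decision rests on it: 90 was set by recruitment capacity, and the Discussion warns that smaller effects may be missed.

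Finally, a reader might conclude that a partially nested model should replace the ANCOVA. Three or four classes cannot estimate the ICC well, and at low ICC the df penalty in step 4 exceeds the bias being corrected.

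The point cannot be set aside as detail left to a fuller plan, because the article itself fixes the primary model, its covariates, the random effect in the sensitivity model and the power inputs.

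**Conclusion.** The concern holds in conditional form. The design is partially nested, and the primary ANCOVA, the sensitivity mixed model and the detectable effect all assume independent participants. If the within-class ICC in BEST is above zero, the perceived-stress standard error is too small and 0.58 too favourable. With 36 completers per arm in 3–4 classes and standard-error inflation only, the detectable effect is 0.59–0.60, 0.64–0.65 or 0.69–0.72 at ICC 0.01, 0.05 or 0.10. Type I error, for inference beyond the classes run, is about 5.5–6%, 7–8% or 9–12%. The omission is certain. Its size is not, because the ICC range is assumed; near 0.01 the effect is minor.

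**What to change.** 1. In Sample size and in the matching Discussion paragraph, state that 0.58 assumes a class ICC of zero. Give the range above, labelled as a known-ICC calculation without df loss. Soften the statement that the trial is powered for effects typical of remotely delivered programmes.

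2. Keep the ANCOVA as primary. Before any access to outcome data, pre-specify a sensitivity analysis giving the perceived-stress confidence interval with the BEST-arm variance inflated at fixed ICCs of 0.01, 0.05 and 0.10, using the actual class sizes. Report the largest ICC at which the result stays significant. With equal arms and class size m this is 2((t/1.995)² − 1)/(m − 1), where t is the observed ANCOVA statistic. Word the efficacy claim accordingly.

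3. A fitted partially nested model with small-sample df is optional and descriptive only.

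**Cost.** Some wording and a few lines of code; class membership is known from delivery. The timeline permits it, since analysis follows the end of data collection in December 2026. The downside is a less favourable stated detectable effect and sensitivity intervals about 2–3% (ICC 0.01), 10–13% (0.05) and 18–25% (0.10) wider than the ANCOVA interval.

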*Mid-Course Assessment (T2).* At the halfway point of the intervention (week 3), all participants will be emailed a link to complete self-report questionnaires assessing only the primary outcome and the mediator variables. The reduced midpoint battery takes approximately 5–10 minutes to complete.

*Post-Intervention Assessment (T3).* All participants will be emailed the post-intervention assessment link and mailed a second blood collection kit to complete both tasks within 2 weeks following the conclusion of the study intervention. The questionnaire will include all study variables. Assessment burden at post-intervention is equivalent to baseline (approximately 20–30 minutes for questionnaires and 10 minutes for blood collection).

*Procedure for Blood Collection, Processing, and Storage.* The Tasso T-20 device [73] will be used to collect, store, and transport capillary blood for testing at the Social Genomics Core Laboratory. The Tasso is designed for use in non-clinical settings with adult populations. After collection, samples will be stored at −20 °C and analyzed in a single batch once data collection is complete.

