#### Secondary outcomes.

Secondary outcomes include depressive symptoms, burnout, psychological well-being, sleep quality, and markers of inflammation. They will be assessed at baseline (T1) and at the post-intervention time point (T3).

*Depressive symptoms*. Depressive symptoms will be based on scores on the 20-item Center for Epidemiologic Studies-Depression Scale (CES-D), a commonly used depression measure [84]. The CES-D is a reliable, validated, and widely used measure that includes central components of depressive symptomatology [84]. Participants respond to twenty statements that assess how often the individual felt or behaved during the past week on a four-point Likert scale from 0 (rarely or none of the time [less than 1 day]) to 3 (most or all of the time [5–7 days]). All 20 items will be summed to provide a total score. The possible range of scores is 0–60, with higher scores indicating a greater frequency of depressive symptoms. The CES-D has frequently been used to assess depressive symptoms in healthcare workers [29,85] and has been shown to be responsive to mindfulness interventions [86].

*Burnout.* Burnout will be measured via the 22-item Maslach Burnout Inventory for Medical Personnel (MBI-M) [87]. Items assess the frequency of personal attitudes and feelings within the past month [87]. The MBI-M measures three components of burnout: emotional exhaustion, depersonalization, and reduced personal accomplishment. Emotional exhaustion is assessed with nine items and refers to feeling emotionally overextended and exhausted by one’s work. Depersonalization is assessed with five items and refers to an impersonal response toward the recipients of one’s services. Personal accomplishment is assessed with eight items and reflects feelings of competence and achievement in work-related pursuits. All items are scored on a 7-point Likert scale from 0 (never) to 6 (every day). Higher scores on the emotional exhaustion and depersonalization subscales correspond to a greater experience of burnout. The personal accomplishment subscale is positively worded; therefore, a one-item increase corresponds to a greater experience of work-related efficacy. Each subscale will be summed to provide total scores for emotional exhaustion, depersonalization, and personal accomplishment. The MBI-M has been validated in several samples of healthcare workers [88,89] and has been shown to be sensitive to psychosocial intervention effects [90].

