*Feasibility and acceptability.* Analyses of feasibility and acceptability will be primarily descriptive and will be evaluated against the pre-specified benchmarks described above. Feasibility will be summarized as the number of participants recruited during the recruitment period, the proportion retained through the post-intervention assessment, and session attendance. Attendance will be reported as the number of sessions attended (including the full distribution across participants) and as the proportion of participants who meet the completion threshold of at least three of six sessions. Acceptability will be summarized using mean Treatment Satisfaction Questionnaire (TSQ) scores, evaluated against the pre-specified acceptability benchmark, together with the dimension-specific ratings from the optional feedback form (overall quality, relevance, clarity of instruction, and pacing/structure), reported separately to characterize distinct components of acceptability. The open-ended feedback form responses will be summarized qualitatively to identify specific features that participants found more or less acceptable. Where sample size permits, feasibility and acceptability will additionally be summarized across relevant subgroups (e.g., specialty) to examine heterogeneity. These subgroup summaries will be descriptive and exploratory.

*Primary and secondary outcomes.* All analyses will employ an intention-to-treat (ITT) principle. Thus, regardless of how many classes they attended or assessments they completed, all randomized participants will be included in analyses and analyzed based on their original group assignment [133]. When possible, we will record the reasons for discontinuing participation, properly annotate them in the CONSORT diagram, and retain the data for potential exploratory subgroup analyses.

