As a complementary, pre-specified sensitivity analysis under a missing-at-random assumption, a linear mixed model will be fit using all available data from all randomized participants with at least one post-baseline observation, with fixed effects for condition and time (categorical) and a random intercept for participants. The between-condition contrast at the post-intervention endpoint will be extracted from this model to correspond to the primary estimand, and change over time and the condition-by-time interaction will be examined as secondary, descriptive analyses [136,137]. As an additional sensitivity analysis, we will repeat the primary outcome models using a per-protocol approach, restricting to participants in the BEST condition who attended at least three of the six intervention sessions (and the corresponding WLC participants), to assess whether the intervention effect differs among those who received the intervention as intended. Since a per-protocol analysis does not preserve the original randomization, it will be interpreted as a complementary, exploratory analysis rather than a confirmatory test of the ITT result. Lastly, because the analyzable sample is modest, the trial is not powered for formal moderation or subgroup analyses. Any examination of whether intervention effects differ across physician subgroups (e.g., specialty) will be exploratory and hypothesis-generating, intended to inform future adequately powered trials rather than to provide confirmatory tests. All tests, primary and secondary outcomes, will be two-sided with an alpha level of 0.05. All analyses will be conducted in R version 4.4.3 [71].

*Mediation analyses.* Mediation analyses will be conducted using the PROCESS macro in R [138]. To enhance the temporal precedence of the intervention’s effect on perceived stress through each mediator, we will assess the outcome (perceived stress) and mediators (compassion, positive emotions, equanimity/mindfulness) for all participants at the midpoint of the six-week intervention (T2). We will fit a parallel mediation model that includes group assignment (BEST vs. WLC) at T1 as the predictor variable, compassion, positive emotions, and equanimity/mindfulness at T2 as the mediators, and PSS scores at T3 as the outcome. The model will control for T1 perceived stress and for each mediator’s T1 values.

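### The mixed-model sensitivity analysis excludes randomized participants with no post-baseline observation, which conflicts with the all-randomized rule and can bias this check when baseline-related dropout differs by arm

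*Protocol article*

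**What the plan says.** Under Primary and secondary outcomes, the Data analysis plan sets a general rule: "All analyses will employ an intention-to-treat (ITT) principle". It spells this out: "regardless of how many classes they attended or assessments they completed, all randomized participants will be included in analyses". The primary ANCOVA follows the rule by using multiple imputation for missing endpoint values, on the assumption that data are missing at random given baseline covariates and observed outcomes.

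The same section then adds a sensitivity analysis under that assumption, a linear mixed model fitted to the available data from "all randomized participants with at least one post-baseline observation". It lists fixed effects for condition and for categorical time, and a random intercept. Its purpose is also stated: "The between-condition contrast at the post-intervention endpoint will be extracted from this model to correspond to the primary estimand". The per-protocol analysis that follows is openly described as departing from randomization. The mixed model carries no such label.

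The schedule matters here. Under Procedures and study flow, the T2 questionnaires are described as "assessing only the primary outcome and the mediator variables". The Secondary outcomes section and Table 1 place burnout, depressive symptoms, well-being, sleep and the inflammatory measures at T1 and T3 only. The Abstract and the text under Fig 2 suggest a mid-course measurement of all outcomes; the working below follows the detailed schedule.

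**The concern.** A set defined by having a post-baseline observation depends on which assessments were completed, and the general rule says that does not matter. That is a conflict between two stated rules, not a detail left to a fuller document.

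It also has a statistical consequence. When baseline is one of the responses, the baseline record of someone who withdraws tells the likelihood how that arm's completers differ from the arm as randomized. Deleting the record removes that correction. The check could then differ from the imputed ANCOVA because of its analysis set alone, or could seem to support an effect seen only in completers.

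**Working it through.** **1. The plan's own figures.** The Sample size section gives 90 randomized, about 19% attrition, about 72 complete, a baseline-post correlation r = 0.50 and a minimum detectable effect d = 0.58. Check: 90 × 0.81 = 72.9. For an ANCOVA with N = 72, one covariate, two-sided α = 0.05 and 80% power, the noncentral F gives f = 0.3349, so d = 2 × 0.3349 × √(1 − 0.25) = 0.580. The figure reproduces, so N = 72 and r = 0.50 are used below.

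**2. Who is removed.** Take 90 − 72 = 18 dropouts and let s be the share who leave before T2 (not given; assumed 0 to 1).

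- PSS: N = 90 − 18s. This is 90 at s = 0, 81 at s = 0.5 and 72 at s = 1.
- A T1/T3 outcome, if the model is applied to it and the clause is counted per outcome: a post-baseline observation can only be T3, so N is about 72 whatever s is. About 18 of 90 (20%) are excluded.

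**3. Effect on the T3 contrast for a T1/T3 outcome.** Assume SD 1, no true effect, dropout depending only on the T1 value (so missing at random), and a mean for each arm at each visit. Let m be the mean T1 value among an arm's completers, relative to the mean of all randomized.

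- Baseline-only records deleted: each arm's T3 estimate is its completers' raw mean, with expectation r × m. Bias = r × (m_BEST − m_WLC).
- Baseline-only records kept: each arm's estimate becomes the completers' T3 mean plus r × (0 − m). The two terms cancel and the bias is 0.

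**4. Numbers at r = 0.5.** The dropout patterns are assumptions, since the documents give none. The slope is the change in log-odds of dropout per baseline SD.

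| Dropout pattern | Bias, records deleted | Bias, records kept |
|---|---|---|
| Random in both arms, or same slope and rate in both | 0.00 | 0.00 |
| BEST slope 0.5, waitlist random | −0.04 to −0.05 | 0.00 |
| Slope 0.5 in both arms, attrition 29% BEST and 10% waitlist | −0.04 | 0.00 |
| BEST slope 1, waitlist random, about 19–22% attrition | −0.08 to −0.10 | 0.00 |
| BEST slope 1, waitlist random, attrition 29% and 10% | −0.12 | 0.00 |
| BEST slope 1, waitlist slope −0.5 | −0.13 to −0.14 | 0.00 |

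Example: a bias of −0.12 means completers' baselines differ by −0.12 / 0.5 = −0.24 SD between arms. The sign follows the assumed direction and would reverse if low scorers left BEST.

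Bias is proportional to r. Over the protocol's range for PSS, r = 0.40 to 0.60, the span becomes −0.04 × 0.8 = −0.03 to −0.14 × 1.2 = −0.17.

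**5. At trial size.** This used 3,000 simulated trials, 45 per arm, true effect −0.50 and about 19% dropout. With random dropout or the same baseline dependence in both arms, both versions of the model give about −0.50. With opposite slopes of 0.8 and −0.8, the restricted model gives −0.634 and the unrestricted −0.506, a gap of 0.128. With the extreme slopes 1.5 and −1.5 they give −0.715 and −0.507, a gap of 0.208, beyond the range in step 4.

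**6. PSS.** Anyone seen at T2 stays in the model. If all dropout falls after T2, the clause removes nobody and changes nothing. The sizes in step 4 carry over to PSS only if all dropout occurs before T2.

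**The case against.** The strongest reply concerns the model. The plan says outcome models adjust for a fixed set of covariates. If baseline were a covariate in the mixed model, a participant with only a T1 value would add nothing, and the clause would merely describe who has data. Adjusting the same completers for baseline brings the bias to 0.00 in the dropout scenarios rerun. So it would be wrong to infer that a mixed model is valid under missing at random only when baseline-only records stay in. This point stands. It does not settle the matter, because the sentence on baseline adjustment names the ANCOVA, while the mixed model lists only condition and time. For a T1/T3 outcome, moreover, baseline as covariate leaves one record per person, and a random intercept could not be estimated.

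A reader might also infer that every secondary outcome is certain to be analysed in completers only. The text does not go that far. It does not say that the mixed model covers secondary outcomes, although the paragraph heading implies it. Nor does it say that the post-baseline observation is counted outcome by outcome. If any post-baseline response qualified, someone with a T2 PSS would keep a baseline depression score in the model.

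The bias should not be expressed as a share of the 0.58 minimum detectable effect. That figure is defined for PSS, whereas the step 4 sizes describe a T1/T3 outcome. With about 36 per arm, the standard error of a raw T3 contrast is √(2/36) = 0.24 SD, so 0.04 to 0.14 SD is roughly 0.2 to 0.6 standard errors. Nothing in the documents predicts dropout that differs by arm.

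**Conclusion.** The conflict between the two rules holds on the text alone. As the mixed model is written, with baseline as a response, the restriction also works against its role as a missing-at-random check on the primary estimand.

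The size is conditional. PSS retains 72 to 90 of 90. A T1/T3 outcome retains about 72, provided the model is applied to it and the clause is counted per outcome. For such an outcome the T3 contrast is biased by about −0.04 to −0.14 SD at r = 0.5 when baseline-related dropout differs between arms in strength or rate. It is unbiased when dropout is random or the same in both arms. These figures rest on assumed dropout patterns and on visit-specific arm means.

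A reader might take this as a threat to the trial's main result; the documents do not support that. The single confirmatory test is the PSS ANCOVA with multiple imputation, which keeps everyone randomized. The secondary outcomes are declared exploratory. This is a minor to moderate correction to a sensitivity analysis.

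**What to change.** In the mixed-model sentence, replace "all randomized participants with at least one post-baseline observation" with wording that admits every randomized participant who has any recorded value of the outcome being analysed, and state that baseline is one of the responses. The sentence then agrees with the general intention-to-treat rule. State also which outcomes the model covers.

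The cost is one clause in the plan and a dated note to the preregistration. No new data are needed, because baseline is completed before participants learn their assignment. Data collection is planned to run to December 2026, and the principal investigator has committed not to access outcome data for analysis before it ends, so the change can still be declared as a pre-analysis amendment.
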